### Participant Timeline

Participants will enroll and participate fully remotely from an electronic device. The participant timeline includes a Baseline Phase (up to 1 week), Sampling Phase (2 weeks), Switching Phase (12 weeks), and Observation Phase (14 weeks) for a total of up to 29 weeks.

Participant time commitment:

- Verbal Screening/Consent/Orientation: 25 minutes
- Baseline Survey: 25 minutes
- Pre-sampling call/Review of study kit: 30 minutes
- Product sample survey, first 6 weeks: 5 minutes
- Post-sampling survey: 25 minutes
- Post-sampling phone call: 10 minutes
- Product sample survey, second 6 weeks: 5 minutes
- Mid-switch survey: 25 minutes
- Mid-switch phone call: 10 minutes
- Post-switch survey: 25 minutes
- Observation survey: 25 minutes
- Debrief phone call: 10 minutes

Total time commitment: 220 minutes (3 hours, 40 minutes)

### Duration of Study

We anticipate the clinical trial to take 5 years to complete. The groundwork for data collection will take place in Y1, recruitment and enrollment activities will take place in years 1, 2, 3, and 4, and data analysis will be the focus in year 5.

**Alternatives to Participation**

They may choose not to participate without penalty or loss of benefits to which they are otherwise entitled.

# **4. Institutional Approvals**

| Check all institutional approvals that apply to research being conducted at Ohio State. |
| --- |
| Comprehensive Cancer Center (CCC) Clinical Scientific Review Committee (CSRC): Approval or exemption required prior to IRB review for all cancer-related research.  Provide a copy of the approval letter on the Other Files page of the smart form. |
| Institutional Biosafety Committee (IBC):  Approval required prior to IRB review for research involving biohazards (recombinant DNA, infectious or select agents, viruses, toxins), gene transfer, or xenotransplantation.  Provide a copy of the approval letter on the Other Files page of the smart form. |
| Human Subject Radiation Committee (HSRC):  Approval required for research involving radiologic procedures for research purposes (e.g., non-clinical care X-rays, DEXA or CT scans, nuclear medicine procedures).  Complete the Radiation appendix and provide a copy of the HSRC approval letter if available. |

# **5. Participant Population**

| Specify the participant population(s). Check all participant groups that apply. For any population other than adults, complete the applicable appendix. |
| --- |
| Adults with impaired decision-making capacity  Children  Neonates of uncertain viability  Nonviable neonates  Non-English speaking individuals  Pregnant women/fetuses (only if pregnant women will be intentionally recruited and/or studied)  Prisoners |

We will recruit 1000 participants from the 180 rural counties in the Appalachian region. In alignment with the Appalachian Regional Commission,^8^ we will use Urban Influence Codes (UICs) from the United States Department of Agriculture and Office of Management and Budget to identify rural counties; counties with a UIC > 6 will be eligible for inclusion.

## Inclusion/Exclusion Criteria

| ***Inclusion and Exclusion Criteria*** | |
| --- | --- |
| **Inclusion** | **Exclusion** |
| Read and speak English | Report currently using smoking cessation medications, NRT, or actively seeking treatment for smoking cessation |
| 21 years or older | Use of ONPs in past 3 months |
| Smoke ≥5 cigarettes per day for the past year | Use of Nicotine Replacement Therapies in past 3 months |
| Willing to use ONPs or NRT | Use of other tobacco products >10 days/month |
| Live in rural Appalachian county | Unstable or significant medical condition |
| Have a smartphone and/or willing to use a smartphone for study purposes (smartphones may be provided to participants for study purposes only); willing to download a free app for the study | Unstable or significant psychiatric conditions (past and stable conditions will be allowed) |
| If capable of becoming pregnant, verbal confirmation of not being pregnant based on urine pregnancy test results | History of cardiac event or distress within the past 3 months |
| Willing to blow air into a handheld study device | Currently pregnant, planning to become pregnant within 6 months, or breastfeeding |
|  | Live in same household as another study participant. |

Note: Only participants who complete the baseline assessment, verify themselves as a smoker at the pre-sampling call time-point via iCO ≥7, and confirm they are not pregnant (if capable) will be included as part of the intent-to-treat sample. If the participant’s iCO reading is below 7, study staff will call the participant to ask when they last smoked/when they took the iCO test. The participant may be asked to retake the test at a more typical time if the initial test was unusual, e.g., before the first cigarette of the day.

We are excluding people under the age of 21 due to tobacco and nicotine use being illegal for this age group. We are also excluding pregnant or breastfeeding individuals or those who are not able to produce a negative pregnancy test due to NRT and ONP not being recommended for use during pregnancy. We are excluding participants who do not speak and read English as our study forms are all in English.

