At the conclusion of the Orientation Call, participants will be emailed or texted a link to the baseline questionnaire ***(Survey Message, Baseline Survey).*** The baseline survey will ask which flavors the participant would like to sample. Participants will be asked about both NRT and ONPs since randomization will not have occurred yet. Participants will be asked to complete the baseline survey in 3 days. Study staff will call, email or text (any combination based on participant preferences) participants up to 10 times over the course of two weeks to remind them to complete the survey. ***(Survey Reminder).***

Following completion of the baseline survey, participants will be randomized to one of two arms for a period of 14 weeks (the Sampling and Switch Phases): 1) ONPs or 2) combination NRT. Randomization will occur using a stratified block-randomization procedure with small, random sized-blocks. Randomization will be stratified by self-reported cigarette dependence, sex, and ONP use history (ever vs. never). We will use FTND<5 vs FTND>=5 for the cigarette dependence portion of the randomization.

Study Kits/Products: Following randomization, participants will be mailed their study kits. Study kits will be tailored to each study group. Study kits will include a Welcome Card ***(Welcome Card),*** welcome/thank-you letter ***(Welcome Letter),*** copy of the consent form, ***(NRT / ONP Fact Sheet)****,* study product guidelines ***(NRT / ONP Guidelines)****,* study product troubleshooting tips ***(NRT / ONP Tips),*** nicotine overdose fact sheet ***(Nicotine Overdose Fact Sheet)*,** participant roadmap outlining their involvement in the study ***(Participant Roadmap),*** individual carbon monoxide (iCO) device and instructions ***(iCOquit Instructions),*** pregnancy test for those who can become pregnant, and study product to sample. The study kit will also include the participant’s ClinCard, and information on how to use the ClinCard ***(ClinCard Info Sheet, ClinCard FAQs)*** and information about the referral program ***(Referral Letter, Referral Flyer).***

The ONP Group will receive three flavors based on what they chose on the baseline survey. They will receive 3 mg and 6 mg concentrations in each flavor.

The NRT group will receive 14 mg and 21 mg patches, and they will receive one to three flavors of lozenges based on what they chose on the baseline survey. They will receive 2 mg and 4 mg concentrations in each flavor.

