The Pre-sampling Zoom or phone call will be scheduled for when participants have received their study kits. Reminders about the call will be sent 1-2 days before the scheduled Pre-Sampling Call ***(PreSamp Call Reminder Text, Zoom Instructions Reminder Email).*** The Zoom/call will include study product education, use instructions, and troubleshooting tips. Participants will also complete their first iCO measurement during the pre-sampling call. This measurement will confirm that they are smoker. If the measurement is ≥7 ppm, they will be considered a smoker. If the measurement is less than 7 ppm, they will not be able to participate. During this call, participants will also verbally confirm that they are not pregnant.

Participants will set an agreed upon switch date approximately 2 weeks from the pre-sampling call and will be asked to immediately start using their sample products ad libitum to become familiar with their use. Participants will also be informed that they will receive two additional product shipments, one before their switch day and another ~6 weeks after their switch day. Participants will be asked prior to future shipments what flavors and nicotine concentrations they would prefer to be sent. ***(Pre-sampling Call Script).***

Sampling Phase: Product Sample Survey

The Sampling Phase check-in message/questions will be automatically sent via REDCap (text or email) 6-7 days after the Pre-Sampling Call. The questions will ask participants to choose study product nicotine concentration(s) and flavor(s) for the first ~6 weeks of the Switch Phase. ***(Product Sample Survey)*** If the questions are not completed in 24 hours, the study team will follow-up with a phone call and text and/or email ***(Survey reminder).*** Study staff will call, email or text (any combination based on participant preferences) participants up to 10 times to remind them to complete the survey if they have not completed it within two weeks. The switch phase may be delayed if the participant has a delayed response to the survey.

Sampling Phase: Post-sampling Survey

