### Pregnancy Test

All subjects capable of becoming pregnant will be sent a pregnancy test in the study kit. Each participant will need to verbally confirm that they are not pregnant during the pre-sampling call based on the results of the pregnancy test. If a participant is unable to confirm that they are not pregnant or if they are pregnant, they will not be able to continue with the study.

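### The set called intent-to-treat is selected after randomisation and after the arm is known, so it is not intent-to-treat and the abstinence comparison can be biased in either direction

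*Protocol*

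**What the plan says.** The order of events is set out in the Protocol, section 3.

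- **Randomisation** (Baseline Phase): "Following completion of the baseline survey, participants will be randomized to one of two arms for a period of 14 weeks".
- **Kit** (Baseline Phase, Study Kits/Products): "Following randomization, participants will be mailed their study kits. Study kits will be tailored to each study group". The kit holds the assigned product, the iCO device and, where relevant, the pregnancy test. Participants are not blinded (Randomization, Blinding, and Unblinding).
- **First CO reading** (Pre-Sampling Zoom/Call): "Participants will also complete their first iCO measurement during the pre-sampling call". Staff give study product education on the same call. On a low reading: "If the measurement is less than 7 ppm, they will not be able to participate".
- **Pregnancy** (Pregnancy Test): "Each participant will need to verbally confirm that they are not pregnant during the pre-sampling call based on the results of the pregnancy test". Those who cannot confirm do not continue.

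The Note under the Inclusion/Exclusion Criteria in section 5 then defines the analysis set: "Only participants who complete the baseline assessment, verify themselves as a smoker at the pre-sampling call time-point via iCO ≥7". It adds the pregnancy check as a further condition and gives the label intent-to-treat to the people who pass everything. The same Note has staff call anyone who reads below 7 and adds: "The participant may be asked to retake the test at a more typical time if the initial test was unusual".

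Section 15 names biochemically verified 7-day point prevalence abstinence at week 12 as the primary outcome. For missing data it plans inverse probability weighting, to be compared with an intent-to-treat analysis that it describes as more conservative.

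**The concern.** An intent-to-treat set is everyone randomised, analysed as allocated. Here, membership depends on what people do and what is measured after they know their arm. Three routes could differ between arms:

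- **Attendance.** Someone disappointed with the allocation may not complete the pre-sampling call. Section 1 itself expects ONPs to be the more appealing product.
- **Early use.** Someone who starts the mailed product early and smokes less may read below 7 ppm. Participants are told not to start before the call, but nothing verifies this.
- **Retakes.** The Note lets staff offer a second reading without saying who qualifies or how often. Staff are not said to be blinded, and they give product education on that call, so they very probably know the arm.

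The pregnancy check is unlikely to depend on arm.

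The primary comparison is at stake, and the planned analyses do not clearly protect it. People barred at the call stop participating and so have no week-12 outcome. The intent-to-treat analysis that should account for them leaves them out by definition. The protocol fixes this definition itself, so it is not a detail left to a statistical analysis plan.

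**Working it through.** **Inputs from the protocol (sections 5 and 15).** Abstinence 13% (NRT) and 23% (ONP); two-sided α = 0.05 chi-squared test; 1,000 participants; 80% retention at week 12 (400 per arm) and 70% at the end of the Observation Phase (350 per arm).

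**Reproducing the stated power.** With the pooled two-proportion normal approximation, power is Φ[(d − 1.96·SE₀)/SE₁], where d = 0.10, SE₀ = √(2·0.18·0.82/n) and SE₁ = √(0.13·0.87/n + 0.23·0.77/n). This gives 95.9% at n = 400 and 93.3% at n = 350. The stated figures, over 95% and over 90%, hold. The fault is in the analysis set, not the arithmetic.

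**How exclusion biases the comparison.** The protocol gives no exclusion rate, so the following values are assumed. Let p be the true abstinence rate among all randomised in an arm, e the fraction excluded at the call, and q the abstinence rate of the excluded. The rate among those kept is

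(p − e·q) / (1 − e).

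Take a true null of p = 15% in both arms, 500 randomised per arm and 80% retention, so that 500·(1 − e)·0.8 are analysed per arm.

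| Excluded, NRT / ONP | q | NRT kept | ONP kept | ONP − NRT | Type I error |
|---|---|---|---|---|---|
| 10% / 10% | 30% | 13.3% | 13.3% | 0 | 5.0% |
| 10% / 5% | 30% | 13.3% | 14.2% | +0.9 points | 6.4% |
| 15% / 5% | 15% | 15.0% | 15.0% | 0 | 5.0% |
| 15% / 5% | 30% | 12.4% | 14.2% | +1.9 points | 11.2% |
| 15% / 5% | 3% | 17.1% | 15.6% | −1.5 points | 8.4% |
| 20% / 5% | 35% | 10.0% | 13.9% | +3.9 points | 35.5% |

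For the fourth row, NRT is (0.15 − 0.15·0.30)/0.85 = 12.4% and ONP is (0.15 − 0.05·0.30)/0.95 = 14.2%. Swapping the arms' exclusion rates reverses each sign. Equal rates are not a guarantee: with 10% excluded in each arm, but 30% of excluded NRT and 5% of excluded ONP participants abstinent, the bias is +2.8 points and the type I error 18%.

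**Does coding the excluded as smokers repair it?** Keep all 500 per arm and count both the excluded and the 20% lost as not abstinent. The rate per arm becomes (p − e·q)·0.8.

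| Excluded, NRT / ONP | q | ONP − NRT | Type I error |
|---|---|---|---|
| 15% / 5% | 30% | +2.4 points | 25% |
| 20% / 5% | 35% | +4.2 points | 66% |
| 15% / 5% | 15% | +1.2 points | 9% |
| 15% / 5% | 3% | +0.2 points | 5% |

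This rule helps when the excluded have a poor prognosis and makes matters worse in the other three rows. It is not a sufficient remedy alone.

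**Power if 1,000 counts people randomised.** With 10% excluded, 500·0.9·0.8 = 360 per arm remain at week 12 (power 93.9%) and 500·0.9·0.7 = 315 at the end of observation (90.6%). With 15% excluded, the figures are 92.6% and 89.0%.

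**Power for all randomised, missing counted as smoking.** With 20% lost, the rates are 10.4% and 18.4% at 500 per arm (power 95.1%). If 10% also never start, they are 9.36% and 16.56% (power 92.5%).

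**The case against.** - **Late eligibility exclusions can be legitimate.** That holds when eligibility rests on facts fixed before randomisation and judged blind to arm. The iCO reading meets neither condition: it is taken after the product arrives, by staff who very probably know the arm. That staff know it is an inference; the protocol does not say so.
- **There is a safeguard against early use.** The kit section instructs participants not to start before the call. This bears directly on that route and weakens it, but nothing verifies it and it does not touch attendance or retakes.
- **A reader might infer that the randomised comparison is lost.** The documents do not support that. Bias needs exclusions that differ by arm in rate or prognosis. Without any exclusion rate, neither its size nor its sign can be determined.
- **A reader might infer that the two iCO statements flatly contradict each other.** The Note can be read as how an atypical reading is confirmed before the Sampling Phase threshold applies. What stands is that the retake is optional, has no criteria, and should be reconciled with the unqualified rule.
- **A reader might infer that the trial is underpowered.** Section 5 says each subject must meet the criteria, so 1,000 may be counted after the checks. The shortfall arises only if it counts people randomised; even then, at 10% exclusion, the Observation Phase claim of over 90% is still met.
- **Inverse probability weighting is named first.** True, but section 15 does not say which set it covers.

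**Conclusion.** The point stands: the set defined in section 5 is not intent-to-treat, because it is selected on attendance and measurements that follow a known allocation. The comparison of abstinence can be biased either way. The illustrations run from no bias, through +1.9 points (type I error 11%) and −1.5 points (8%), to +3.9 points (about 36%) in the most extreme case tried. All rest on assumed exclusion rates and assumed abstinence among the excluded, under a true null of 15% with 80% retention.

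Power is secondary. Only if 1,000 counts people randomised can the week-12 claim of over 95% be missed (93.9% at 10% exclusion).

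This should be fixed before the trial proceeds further: it affects the primary endpoint of an open-label trial, and outcomes never collected from excluded people may not be recoverable.

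**What to change.** 1. Define the intent-to-treat set as everyone randomised, in the allocated arm, and use it for H1b and H3a.
2. Send the already planned week-12 and end-of-observation surveys and iCO to everyone randomised who has not withdrawn consent, including those who miss or fail the pre-sampling checks. This changes follow-up only, not who may use study product.
3. Where outcomes are still missing, do not rely on missing = smoking alone. Report it alongside the inverse-probability-weighted analysis, with the weighting applied to all randomised.
4. Keep the present section 5 set as a sensitivity analysis, and report post-randomisation exclusions and reasons by arm.
5. Apply one retake rule to every reading below 7 ppm regardless of arm, and make the Sampling Phase text and the section 5 Note agree.

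Alternatively, do the iCO and pregnancy checks before randomisation. That removes the problem at source but changes the procedure, because the device and the test now travel in the arm-specific kit.

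The cost is protocol wording, a few extra follow-up contacts and some dilution: power of about 92.5% instead of about 95.1% if 10% never start and all missing count as smoking. The result still depends in part on the missing-data assumption.

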#### Inclusion of Women and Minorities

Women will be included in the project. Currently, women represent approximately 50% of smokers. Our lab has traditionally recruited approximately 50% of its sample as women when recruiting adult smokers, and we expect that to be the case here. If the share of either sex in our sample exceeds 55% during accrual, we will pause recruitment advertisements to the over-represented sex to improve balance within our sample.

Participants from racial and ethnic minority groups will be included. Participants will be recruited from the 180 rural Appalachian counties in the US. According to the 2020 US Census, the racial and ethnic distribution in Appalachia is 80.3% white non-Hispanic, 10.0% Black non-Hispanic, 5.6% Hispanic (any race), and 4.1% other race, non-Hispanic.^8^ We will target enrolling a sample that closely matches the racial and ethnic distribution of the Appalachian region. We will continuously monitor enrollment to ensure we are meeting recruitment goals to avoid under-recruiting minority race and ethnicity participants. If the targeted enrollment for minorities is not met because they do not respond to the advertisements, we will make special efforts to increase their participation by advertising in community newspapers, community centers, and working with the OSU Comprehensive Cancer Center’s Center for Cancer Health Equity (<https://cancer.osu.edu/our-impact/community-outreach-and-engagement/center-for-cancer-health-equity>). We will also pause recruitment advertisements to over-represented groups as needed to improve balance in our sample. We will require that no more than 82% of our sample is white non-Hispanic.

**Number of Participants**

We expect up to 1,000 participants to enroll in this study. Each subject must meet I/E criteria.

Assuming 80% retention at the end of the 12-week Switch Phase, a total sample of 800 participants (400 per arm), will provide greater than 95% power to detect a difference in smoking abstinence between the NRT and ONP arms for a two-sided, a=0.05 level chi-squared test. Further assuming 70% retention at the end of the 14-week Observation Phase, a sample of 700 (350 per arm) will provide over 90% power to detect significant difference between the ONP and NRT arms.

All study activities will take place remotely using participants’ study devices.

**Participant Identification**

Leveraging various recruitment methods, we will recruit participants from the 180 rural counties in the rural Appalachian region. In alignment with the Appalachian Regional Commission, we will use Urban Influence Codes (UICs) from the United States Department of Agriculture and Office of Management and Budget to identify rural counties; counties with a UIC > 6 will be eligible for inclusion.

We will identify participants through following recruitment methods:

1. Online Advertising
2. Referrals
3. Lung Cancer Screening Activities
4. Community Organizations
5. Marketing Emails
6. Contacting participants from other studies
7. Newspapers
8. Webpage
9. Referrals
10. Respondent Driven Sampling

Online Advertising

We will utilize platforms including but not limited to Meta (ex. Facebook, Instagram), Google (ex. YouTube, ads), online advertising, and TikTok for recruiting. ***(Social Media; BC Ad Copy, Feed, Landing Page, Screening Form, Snapchat, Video 1, Video 2, Video 3, Video 4)***

Lung Cancer Screening Activities

Study information will be shared via lung cancer screening activities, such as lung cancer screening vans visiting areas of Appalachia. ***(Flyer)***

Community Organizations

We will work with local community groups and or organizations, such as community coalitions and local health departments, to promote the study. ***(Flyer) (Ads)***

Marketing Emails
Study staff will work with agencies who are able to promote the study via marketing emails. ***(Flyer) (Ads)***

Contacting participants from other studies

Study staff will contact participants from other studies who have consented to be contacted about additional studies. ***(Recruit Email) (Recruit Text)***

Newspapers

Ads will be utilized in local newspapers (print and online) to promote the study. ***(Ads)***

Webpage

There will be a study webpage ***(Webpage)*** with information, including the link to the online screening survey.

Referrals
Study participants may share study information with others who may be interested. ***(Flyer)***

Respondent Driven Sampling

Subjects will also be recruited through respondent-driven sampling (RDS), which is commonly used in studies involving contact tracing and social networks (e.g., sexual health studies). This sampling method is a type of peer-driven chain-referral sampling (Heckathorn 1997, 2002). Although there are biases associated with chain-referral sampling that can affect the composition of the sample achieved, RDS can control these biases through its methods of data collection and analysis. RDS initial recruiters who are study subjects will recruit future subjects (seeds) who in turn recruit other subjects (seeds). This chain of recruiters and recruits then continues for multiple “waves” of recruitment. Ongoing recruitment is fostered with a dual incentive system: one incentive for participating in the project and another incentive for each person recruited. Recruiters are linked to their seeds by a unique number or code on recruitment coupons/flyers, and they are limited in how many people they can recruit. The identity and status of individuals who may have provided RDS codes/coupons will not be disclosed. The seeds who meet the eligibility can choose to participate in the study or not. Referring individuals to the study is optional. Subjects’ participation in the study will not be affected if they do not invite others or if those they invite do not meet the criteria outlined above. Participants will be provided with referral information in their study kits including their codes ***(Referral Flyer, Referral Letter).*** Participants can share the ***ARISE Referral Image*** with people they believe may be interested and a good fit for the study. We may share the referral image via email or text. We may also share the referral program information via email ***(Referral Email).*** Their referral code will be linked to their record and the payment will be made. Participants can $10 for each 21+ year old smoker they refer. To be eligible for referral compensation, the person referred must complete the online and verbal screeners. Participants can earn up to $50.

We have significant experience conducting large, nationwide, trials of alternative nicotine products. Co-I [name] has led 5 state- or nationwide remote trials of NRT (Ns=616, 849), one nationwide, remote trial of snus (N=1236), and one remote trial of electronic cigarettes (R01CA210625). MPI [name] is a Co-I on the electronic cigarette trial. MPI [name] ([name] is a Co-I) also recently completed accrual for a remote, randomized trial (U01DA045537) comparing electronic cigarettes vs. NRT on smoking outcomes among recent tobacco Quitline treatment failures from two states (Oklahoma and South Carolina). This study recruited 350 participants within 18 months with 80% retention. Each of these studies demonstrates our ability to recruit large numbers of smokers, distribute products efficiently via mail, and complete follow-up assessments with strong retention.

